# Oral flucloxacillin and phenoxymethylpenicillin versus flucloxacillin alone for the emergency department outpatient treatment of cellulitis: study protocol for a randomised controlled trial

**DOI:** 10.1186/1745-6215-14-164

**Published:** 2013-06-03

**Keywords:** Cellulitis, Adult, Flucloxacillin, Phenoxymethylpenicillin, Penicillin V, Oral, Randomised controlled trial, Double blind, Emergency department

## Abstract

**Background:**

Oral flucloxacillin, either alone or in combination with phenoxymethylpenicillin, is a commonly prescribed antibiotic for the treatment of cellulitis, particularly in Ireland and the United Kingdom. This study aims to establish the non-inferiority of oral monotherapy (flucloxacillin alone) to dual therapy (flucloxacillin and phenoxymethylpenicillin) for the outpatient treatment of cellulitis in adults.

**Methods/design:**

This study is a multicentre, randomised, double-blind, placebo-controlled trial of adults who present to the emergency department (ED) with cellulitis that is deemed treatable on an outpatient basis with oral antibiotics. After fulfilling specified inclusion and exclusion criteria, informed consent will be taken. Patients will be given a treatment pack containing 7 days of treatment with flucloxacillin 500 mg four times daily and placebo or flucloxacillin 500 mg four times daily and phenoxymethylpenicillin 500 mg four times daily. The primary outcome measure under study is the proportion of patients in each group in which there is greater than or equal to a 50% reduction in the area of diameter of infection from the area measured at enrolment at the end-of-treatment visit (7 to 10 days). Secondary endpoints include a health-related quality of life measurement as rated by the SF-36 score and the Extremity Soft Tissue Infection Score (not validated), compliance and adverse events. Patients will be followed up by telephone call at 3 days, end-of-treatment visit (EOT) at 7 to 10 days and test-of-cure (TOC) visit at 30 days. To achieve 90% power, a sample size of 172 patients per treatment arm is needed. This assumes a treatment success rate of 85% with oral flucloxacillin and phenoxymethylpenicillin, an equivalence threshold Δ = 12.5% and an α = 0.025. Non-inferiority will be assessed using a one-sided confidence interval on the difference of proportions between the two groups. Standard analysis including per-protocol and intention-to-treat will be performed.

**Discussion:**

This trial aims to establish the non-inferiority of flucloxacillin monotherapy to dual therapy in the treatment of uncomplicated cellulitis among ED patients. In doing so, this trial will bridge a knowledge gap in this understudied and common condition and will be relevant to clinicians across several different disciplines.

**Trial registration:**

EudraCT Number
2008-006151-42

## Background

Cellulitis is an acute, subacute or chronic inflammation of the dermis and subdermal tissues usually caused by a bacterial infection
[1]. Current use tends to regard the term erysipelas as a form of cellulitis rather than as a distinct entity in which a raised leading edge represents dermal inflammation alone
[2]. Indeed, the terminology used to describe various types of skin and soft tissue infection (SSTI) is complicated because of the use of terms to describe different types of infection (cellulitis, erysipelas, abscess), clinical scenarios (Fournier gangrene) and aetiological agents (‘clostridial myonecrosis’)
[3].

Cellulitis is an understudied condition and the numbers of patients seen and treated in Irish emergency departments (EDs) is unknown. In 2009 in Ireland it accounted for 3,877 hospital admissions resulting in a median hospital length-of-stay (LOS) of 4 days
[4]. In the United Kingdom, one survey showed that it accounted for 3% of emergency visits to a district hospital
[5] and results in approximately 69,576 hospital admissions annually
[6]. In the Netherlands, cellulitis and erysipelas accounted for 3,500 hospitalisations in 1999 to 2001, with an average LOS of 12.1 days
[7]. The population prevalence in the same year was 15.2/100,000 inhabitants, with ten times as many patients treated in the community as in hospital. In the era of community acquired methicillin resistant *Staphylococcus aureus* (CA-MRSA) infection in the United States, outpatient visits for purulent skin and soft tissue infection increased from 32.1 to 48.1 per 1,000 population between 1997 and 2005
[8] with a four-fold increase in hospitalisation rate for cellulitis/abscess between 1999 and 2005
[9]. Cellulitis and erysipelas cost on average €5,300 per hospitalised patient in the Netherlands in 1999 to 2001, with total costs of €13.7 million
[7].

*Staphylococcus aureus* and β-haemolytic Streptococci Lancefield Group A, C and G are the most common causative agents of cellulitis
[10]. In a recent systematic review examining the bacteriological etiology of cellulitis in intact skin, Chira *et al*.
[11] examined 16 trials involving 808 patients. Only 16% had positive cultures, of which *Staphylococcus aureus* was almost twice as commonly isolated as Streptococcus Group A. This finding is especially relevant in North America where the onset of true CA-MRSA infection has reached epidemic proportions
[8,10]. Enterococci are occasionally isolated, usually in patients with leg ulcers, and anaerobic bacteria are the least commonly isolated subgroup and include *Peptostreptococcus* species, *Bacteroides fragilis*, *Prevotella* species, *Porphyromonas* species and *Clostridium* species
[1]. In clinical practice, the majority of these infections can be treated on an outpatient basis with European
[12-14] and North American
[15] prescribing guidelines recommending beta-lactam antibiotics active against gram-positive bacteria. Despite the increase in CA-MRSA, the Infectious Diseases Society of America (IDSA) also still recommends beta-lactam antibiotics for ‘non-purulent’ cellulitis
[15].

Cellulitis is clinically apparent as an area of spreading erythema characterised by warmth, pain and tenderness to palpation. It is on a spectrum of disease from mild infections, easily treatable with oral antibiotics, to severe necrotizing infections with associated high mortality. However, most people are not seriously ill and have a low risk of complications
[16].

### Measures of severity

There are no internationally accepted criteria for ‘mild, moderate and severe’ cellulitis although this classification scheme is widely used in clinical practice
[1]. The classification used by Eron *et al*.
[16], (Table 
1) is useful for guiding treatment decisions for patients with cellulitis. It has been used in local National Health Service (NHS) policy guidelines
[17] and is recommended by the Clinical Resource Efficiency Support Team (CREST) group in Northern Ireland in its consensus statement on the management of cellulitis
[5].

**Table 1 T1:** **Eron classification system for patients with skin and soft tissue infection**[16]

**Class**	**Patient criteria**
**1**	Afebrile and healthy, other than cellulitis
**2**	Febrile and ill appearing, but no unstable comorbidities, or systemically well with comorbidity (PVD, CVI, morbid obesity)
**3**	Toxic appearance, or at least one unstable comorbidity, or a limb-threatening infection
**4**	Sepsis syndrome or life-threatening infection, for example, necrotizing fasciitis

*CVI* chronic venous insufficiency, *PVD* peripheral vascular disease.

The single ‘best antibiotic’ for treating cellulitis is unknown
[1] and thus there is considerable variability in the class, dose and regimen of antibiotic prescribed
[18]. Flucloxacillin either alone or in combination with phenoxymethylpenicillin or its intravenous form, benzylpenicillin, are commonly prescribed in Great Britain and Ireland
[19,20]. Various sources including authoritative textbooks
[21], the national prescribing formulary in the United Kingdom
[22] and local guidelines, provide conflicting information on whether monotherapy with flucloxacillin or dual therapy with combined flucloxacillin and phenoxymethylpenicillin is optimal, particularly for cellulitis treatable on an outpatient basis. Recent evidence has shown that oral phenoxymethylpenicillin prevents cellulitis recurrence in patients with two or more episodes of leg cellulitis
[23].

A study comparing the efficacy, tolerability and compliance of combined oral flucloxacillin and phenoxymethylpenicillin with flucloxacillin alone in the outpatient treatment of cellulitis would provide a valuable resource for clinicians, and may close a gap in the research-based knowledge of this condition.

## Methods/design

### Study aims

To determine whether flucloxacillin monotherapy is non-inferior to combined flucloxacillin and phenoxymethylpenicillin (dual therapy) in the management of Eron Class I and II cellulitis.

### Study design and setting

It is intended to carry out a phase 4, multicentre, active-controlled, double-blind, non-inferiority randomised trial in patients attending the ED with cellulitis deemed clinically treatable with an oral antibiotic as an outpatient (Eron Class I and II cellulitis). Patients will be randomized to receive either flucloxacillin and phenoxymethylpenicillin or flucloxacillin and placebo in a 1:1 ratio.

### Ethical considerations

This study is to be performed in accordance with the Good Clinical Practice (GCP) Guidelines, the EU CT Directive 2001/20.EC, GCP Commission Directive 2005/28/EC, the Declaration of Helsinki (2008) and with all other local regulatory requirements. Risk Analysis was carried out as part of protocol development. The study protocol was approved by Beaumont Hospital Research and Ethics Committee. Patients will be enrolled from the ED they attend. This may be by self-referral or general practitioner (GP) referral.

### Regulatory considerations

The Irish Medicines Board (IMB) is the competent authority for the review and approval of clinical trials with an investigational medicinal product (IMP) in Ireland. The application process for a medicinal trial was successful after formal engagement with the IMB prior to application and during the application process. IMB approval for this trial was granted on 30 January 2009.

### Subject selection

Patients more than 16 years of age satisfying the inclusion and exclusion criteria (Table 
2) who present to the recruiting EDs with cellulitis during the study period, will be eligible for recruitment into the trial. All potential patients will be given time to read the patient information leaflet prior to informed consent being taken. Once consent is signed, the enrolment procedure will continue to random selection of the drug pack. Enrolment will be undertaken by any of the following: a hospital doctor with minimum 2 years experience in Emergency Medicine (including consultants, specialist registrars, associate specialists and non-specialist registrars) and Advanced Nurse Practitioners who are registered prescribers of medications.

**Table 2 T2:** Inclusion and exclusion criteria

**Inclusion criteria**	**Exclusion criteria**
>16 years of age	Any cellulitis that requires intravenous antibiotic
Cellulitis of any body area excluding the perineum, that is treatable with oral antibiotic as an outpatient and in whom either combination of antibiotic is likely to produce a clinical response	Any cellulitis worse than Eron Stage 2 cellulitis
Any two of the following signs:	Pregnancy
1. Erythema	Lactation
2. Warmth	Hypersensitivity to penicillin
3. Tenderness	Chronic skin condition at the site of infection
4. Swelling	Infection involving prosthetic material
5. Regional lymphadenopathy	Thermal injury
Fluency in written and spoken English	Acne vulgaris
	Perineal cellulitis (high risk of anaerobic infection)
	Fungal infection of scalp or nail bed
	Immunodeficiency
	Severe renal or hepatic dysfunction
	Concomitant treatment with oral, parenteral or topical antibiotics at infection site
	Patients taking systemic corticosteroids at a dose exceeding 15 mg (or equivalent) per day for more than 7 days
	Refusal or inability to give informed consent

### Inclusion and exclusion criteria

Inclusion and exclusion criteria are presented in Table 
2.

### Patient randomisation

The randomisation process has been designed by CSTAR (Health Research Board Centre for Support and Training in Analysis and Research), Dublin, Ireland. Trial randomisation codes will be generated by CSTAR. It is intended to use block randomization using a permuted block design with a computer random number generator without stratification, to create two treatment groups of 172 patients (n = 344).

### Randomisation treatments

#### Allocation concealment

A sequentially numbered opaque sealed envelope (SNOSE) will be opened for each patient who consents to enrollment into the study. This envelope will be opaque to intense light. It will contain a copy of the information leaflet, a consent form, an SF-36 and ESTI score, a paper tape measure, the study drugs in two amber containers, and a patient proforma with a unique pre-printed patient identifier to be used throughout the study. The proforma will be inserted in to the ED notes and scanned or stored securely as is standard practice with patient data in the EDs in question. The proforma will then be re-used for the end-of-treatment (EOT) and test-of-cure (TOC) visits. The SNOSEs will be stored in the secure Specialist Registrar Office available in each location, which will be accessible at all times. All study drugs will be packaged by the clinical trial pharmacist who will remain independent of all further patient treatments.

#### Drug appearance

Phenoxymethylpenicillin appears as a circular round white tablet with a marking ‘PEN 500’ on the side (SmPC Athlone Laboratories Limited, Ballymurray, Co. Roscommon, Ireland). The placebo formulation to be used will also be a white round tablet with a notch and contain lactose monohydrate, magnesium stearate and cellulose (FAGRON GmbH & Co. KG [name], Germany. http://www.fagron.de).

Flucloxacillin appears as a caramel coloured, hard capsule marked with ‘FXN 250’ or ‘FXN 500’. Since both groups are receiving flucloxacillin, product blinding is irrelevant.

All efforts will be made to ensure placebo and phenoxymethylpenicillin tablets are similar in appearance; it should be possible to have a dummy inscription on the placebo tablet.

#### Product liability

Public and product liability is in place for licensed medications issued by Athlone Laboratories and includes cover for the generic brands of phenoxymethylpencillin and flucloxacillin to be used in the study.

### Breaking of the study blind

#### On study

If an adverse event is regarded as a potential Serious Unexpected Suspected Adverse Reaction (SUSAR) by the sponsor the treatment group to which the trial subject affected belongs will be unblinded for that subject alone. The procedure will ensure that the identity of the investigational medicinal product (IMP) is only revealed as far as necessary (GCP Directive). All staff will have received training on all aspects of the trial protocol prior to commencement of the trial.

The principal investigator (PI) or authorised member of the team will have a written procedure for requesting randomisation codes for rapidly identifying a blinded IMP in an emergency. Breaking the blind of a trial subject will be at the discretion of the PI, when clinically indicated for the safety of the patient, or in the event of a SUSAR. If the patient needs to be unblinded we will refer to the unblinding SOP for complete details of the procedures to be followed. The master randomisation codes will be kept by the clinical trial Pharmacist and the PI. Unblinding will be performed by the senior clinician/pharmacist when the criteria for a Serious Adverse Event (SAE/SUSAR) have been met and there is a necessity for the PI or treating healthcare professional to know which treatment the patient is receiving to ensure that the patient receives appropriate urgent safety measures.

A 24-hour contact number will be available in the circumstances when unblinding is required. The scenario will be communicated and when the unblinding criteria are met the unblinding will ensue. The PI will document the breaking of the code, and the reasons for doing so, in the site file and in the patient’s medical notes, and in accordance with the clinical trial protocol. If at the EOT visit a clinical failure is apparent and the addition of phenoxymethylpenicillin is felt to be clinically necessary, code breaking will be made possible on a 24-hour basis by making contact with the PI. It is felt that unblinding will be an extremely unlikely event as a treatment failure will more than likely require intravenous antibiotics. Any compromises in blinding will be reported in the trial conclusion.

#### Following completion of the study

Study unblinding will only take place once the statistical analysis plan has been agreed by the trial team and the final database has been locked.

### Study procedure

#### Interventions

##### Wound/skin care

Standard wound care for cellulitis will be permissible in both groups and may include saline soaks and non-adherent dressings. The area of infection will be drawn with a waterproof skin marker and the maximal diameter of the area of infection measured and recorded.

##### Microbiological assay

Whenever possible a specimen for culture and sensitivity will be taken from the infection site at enrolment. This may be from blister fluid or exudate. Specimen results will be made available at follow-up to guide appropriate therapy. Blood cultures will not be taken in this study. Since the expected microbiological yield will be low, a test of microbiological cure will not be used in this study.

##### Therapeutic intervention

Once enrolled patients will be given a 7-day course of either oral flucloxacillin 500 mg four times daily and oral phenoxymethylpenicillin 500 mg four times daily or oral flucloxacillin 500 mg four times daily and oral placebo four times daily.

##### Follow-up

Patients will be telephoned at 3 to 5 days by a study investigator to encourage treatment compliance and EOT visit follow-up. Any deterioration in patient symptoms may be addressed at this visit and a return for clinical assessment may be recommended. The patient will be reviewed at 7 to 10 days after treatment commencement (EOT visit) in the enrolment centre and the area of infection will be measured. At this visit, the patient will be given an SF-36 and ESTI score to complete. A final TOC visit or telephone call will be arranged for 30 days after the enrolment of the patient into the trial.

#### Outcome measures

##### Primary outcome

The primary outcome measure under study is the proportion of patients treated in each group in which there is greater than or equal to a 50% reduction in the maximal diameter of erythema from the area measured at enrolment to that at the end-of-treatment visit (7 to 10 days).

##### Measurement of the primary outcome

Clinical cure: Reduction in the area of cellulitis by ≥50% of the initial diameter.

##### Secondary outcomes

•Clinical failure: a failure of the initial maximal diameter of infection to reduce by ≥50%

•Clinical relapse: initial improvement in cellulitis at the EOT visit followed by a worsening or re-appearance of cellulitis at the TOC visit.

•Quality of life: the SF-36 and the ESTI score at the EOT visit will be measured.

•Compliance with therapy: the number of unused study medications counted at the EOT visit will be measured.

•Adverse Events: all adverse events will be recorded and submitted to the Irish Medicines Board and the Research and Ethics Committee.

•Microbiological profile: the results of specimens sent for culture to receiving laboratories will be profiled.

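### The day-30 relapse outcome ignores antibiotics given for the same cellulitis after the end-of-treatment visit, so re-treatment can mask relapse

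*Protocol article*

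**What the plan says.** The article defines its efficacy outcomes as follows.

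- **Primary outcome:** "greater than or equal to a 50% reduction in the maximal diameter of erythema from the area measured at enrolment", assessed at the EOT visit on days 7 to 10. Measurement of the primary outcome restates it as "Clinical cure: Reduction in the area of cellulitis by ≥50% of the initial diameter".
- **Failure** (Secondary outcomes) is the complement, again by size alone: "Clinical failure: a failure of the initial maximal diameter of infection to reduce by ≥50" per cent.
- **Relapse** (Secondary outcomes): "Clinical relapse: initial improvement in cellulitis at the EOT visit followed by a worsening or re-appearance of cellulitis at the TOC visit".
- **Other secondary outcomes:** "Quality of life: the SF-36 and the ESTI score at the EOT visit will be measured"; compliance is "the number of unused study medications counted at the EOT visit will be measured", which covers study drug only.

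None of these mentions a further or non-study antibiotic.

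Three other sections bear on the point. Microbiological assay says "Specimen results will be made available at follow-up to guide appropriate therapy", without limiting this to failures. Breaking of the study blind allows the code to be broken at the EOT visit if there is a clinical failure and phenoxymethylpenicillin is thought necessary; it adds that intravenous antibiotics are the likelier course in a failure. Sample size, power and statistical methods applies the non-inferiority assessment to the secondary outcomes as well as the primary one. The day-30 contact may be remote: "A final TOC visit or telephone call will be arranged for 30 days after the enrolment of the patient into the trial".

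**The concern.** Study drug lasts 7 days, and cure requires only a 50% reduction, so a patient can be scored a cure at EOT with visible cellulitis. If that patient is given another course, relapse at day 30 is judged after the second course, and the definition takes no notice of it. Relapse then measures the outcome of two treatments under a label that suggests one.

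This matters more in a non-inferiority trial than in a superiority trial, because dilution favours the conclusion being sought. If monotherapy left more residual infection and so led to more re-treatment, its relapse rate would be held down and the arms would look alike. The Data analysis section is itself wary of bias towards similarity and relies on the per-protocol set as a safeguard. The criteria stated for that set are completion of the course and adherence to the protocol. A patient who finished 7 days and was then re-treated is not clearly excluded.

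**Working it through.** **1. The plan's own figure.** Inputs from Sample size, power and statistical methods: success 85%, margin 12.5 points, one-sided α = 0.025, power 90%.

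n per arm = 2 × 0.85 × 0.15 × (1.960 + 1.282)² / 0.125² = 171.5, rounded up to 172. This reproduces the stated 172, and power at 172 is 90.1%. The sample size is not in question.

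**2. Can a cure leave residual infection?** Yes. Halving the diameter leaves 0.5² = 25% of the area for a similar shape. If the criterion is read as area, √0.5 = 71% of the diameter may remain. For example, a lesion going from 20 cm to 9 cm has lost 55% of its diameter and is a cure.

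**3. How are re-treated patients scored?**

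| Patient | At EOT | At day 30, if the further course works |
|---|---|---|
| ≥50% reduction, no further antibiotic | cure | no relapse |
| ≥50% reduction, further antibiotic at EOT | cure | no relapse |
| Some reduction but <50%, antibiotic added | failure | no relapse, although improved at EOT |

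The first two rows cannot be told apart. The third arises because relapse starts from improvement, which is not defined as meeting the cure criterion. It also has a one-sided element: adding phenoxymethylpenicillin supplies something new only to the monotherapy arm.

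**4. Effect on relapse.** In arm k, let q_k be the day-30 relapse risk without further antibiotics, u_k the share re-treated, and e the proportion by which a further course lowers the risk. Taking re-treated patients to be of average risk, recorded relapse is q_k(1 − u_k·e). The recorded difference, monotherapy (M) minus dual therapy (D), is

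(q_M − q_D) − e(q_M·u_M − q_D·u_D).

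If q_M ≥ q_D and u_M > u_D, the second term is positive and hides part of any excess relapse on monotherapy. If u is equal in both arms, a real difference shrinks by the factor (1 − u·e) and a null difference stays null. If re-treatment were commoner on dual therapy, the error could run the other way. The article gives no value for q, u or e, so this shows a direction and not a size.

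**5. What the cure label does not distinguish.** Assume 85% size-based cure in both arms, with a share r of cures re-treated at EOT. Cure without further antibiotic is 0.85 × (1 − r).

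| r, dual | r, mono | Dual | Mono | Difference |
|---|---|---|---|---|
| 10% | 10% | 76.5% | 76.5% | 0 |
| 10% | 15% | 76.5% | 72.25% | 4.25 points |
| 10% | 20% | 76.5% | 68.0% | 8.5 points |

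The size-only difference is 0 in every row.

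**6. Power on the stricter measure.** At 76.5% in both arms, SE = √(2 × 0.765 × 0.235 / 172) = 0.0457. Power = Φ(0.125/0.0457 − 1.960), about 78%. Restoring 90% would need 242 per arm.

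**The case against.** Several stronger readings are tempting, and the article does not support them.

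- **That the primary result is biased towards non-inferiority.** It is not. An antibiotic prescribed after the lesion is measured at EOT cannot change that measurement, and non-inferiority on the primary outcome rests on it in both analysis sets.
- **That a re-treated patient is barred from counting as a relapse.** No such rule exists. Someone who worsens or recurs by day 30 despite further antibiotics still meets the definition.
- **That continuing illness is invisible in every efficacy outcome.** SF-36 and ESTI at EOT may partly reflect residual illness, although neither records a need for antibiotics.
- **That the protocol describes re-treating cured patients.** The code-breaking text concerns clinical failures, who are already non-cures, and calls unblinding very unlikely. The microbiology text does not exclude cures, but cultures are taken only when possible and a low yield is expected. Re-treatment of a cure is permitted, not described.
- **That 8.5 points is an estimate.** It is arithmetic on assumed rates for an endpoint the plan does not use. If monotherapy cleared infection more slowly, fewer patients would normally reach 50% by days 7 to 10, and the primary outcome would show part of that. Holding both arms at 85% switches that signal off.

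Two further objections have weight. A lesion-size endpoint is a legitimate choice in a double-blind trial, and prescribing decisions bring in clinician discretion; that is a reason to leave the primary definition alone. The proforma and full protocol are not shown, so antibiotic use may already be recorded. If so, less needs to be changed, but the relapse definition as stated still does not use that information.

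**Conclusion.** The point holds for relapse. As written, the definition takes no account of antibiotics given for the index cellulitis between EOT and day 30, in a protocol that anticipates therapy decisions at follow-up and assesses non-inferiority on its secondary outcomes. Re-treatment makes a recorded relapse less likely, and if it is commoner in the arm with more residual infection, the comparison is diluted towards no difference.

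For the primary outcome the consequence is one of interpretation only: a cure that was re-treated is not distinguished from one that needed nothing more.

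The size is unknown because the article gives no re-treatment rates. On the assumptions shown, the undistinguished difference in cure without further antibiotics runs from 0 to 8.5 points against a margin of 12.5. This is a worthwhile, cheap improvement to a secondary outcome and does not invalidate the primary test.

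**What to change.** 1. Among patients who meet the cure criterion at EOT, define the day-30 outcome as worsening, re-appearance, or any further antibiotic for the index cellulitis from the EOT visit to day 30. Restricting it to EOT cures keeps EOT failures from being counted again as relapses.
2. Report further antibiotic use for the index infection by arm, with date and reason. If the proforma does not already hold this, add one item; it can be asked by telephone at day 30.
3. As a sensitivity analysis of the primary endpoint, in the ITT and per-protocol sets, report the proportion with at least a 50% reduction and no further antibiotic for the index infection at EOT. Leave the primary definition unchanged.

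The cost is at most one form item and one extra analysis. The stricter measure depends partly on clinician discretion, gives a lower success rate and has less power: about 78% at 172 per arm if 10% of cures are re-treated in both arms. It should be read as supportive and not as a second test with 90% power. The change concerns how outcomes are scored and has no bearing on how patients are treated.
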